## **3. Study Design**

This study is a randomized, controlled, double-blind, study of healthy term formula fed (FF) infants. In the first phase of the study, FF infants will be randomized to receive either a new infant formula formulated for healthy term infants (BBN-001 w/ OPN) or a commercially available infant formula for healthy term infants (Brand Formula). After completion of the first phase, the second phase of the study will randomize infants to receive either BBN-102 w/o OPN or Brand Formula. Infants will consume the formula for a total of 16-weeks; infant growth, serum markers of inflammation, and tolerance to the formulas will be assessed throughout the four-month study period.

The study duration from Day 1 through the EOS visit is approximately 120 days. Each infant will be screened for all inclusion and exclusion criteria. If an infant complies with all inclusion and exclusion criteria and the parent(s)/guardian(s) sign the IRB-approved

Informed Consent Form (ICF), the infant will be randomized to receive a study formula and assigned a unique subject number. If the infant does not comply with one or more of the inclusion or exclusion criteria, the infant will be defined as a screen failure.

Nine visits are scheduled at 15-day intervals with a 3-day visit window.

A flowchart of the study visits is included on the following page.

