## 11.2. Gastrointestinal Tolerance

Gastrointestinal tolerance (stool composition, number of stools per day, stool consistency, fussiness, gas, Infant Characteristics Questionnaire (ICQ) scores) will be compared between BBN-102 w/o OPN and Brand Formula. The studentized residuals for each endpoint will be assessed for normality using a histogram and quantile-quantile plot. If the normality assumption holds, then the gastrointestinal characteristic or general disposition score will be summarized by formula group and visit with descriptive statistics. Treatment effect will be compared using a mixed-effect model for repeated measures (MMRM) with sex, age, baseline value, formula, pooled site, visit, formula by pooled site interaction, and formula by visit interaction as factors. The covariance matrix will be chosen based on the AIC criteria to choose the covariance matrix that best fits the model. In addition, the formula effect by visit will be summarized. An alpha level of 0.05 will be used to test the formula effect. 95% confidence intervals and p-values will be reported on the difference of least square means for comparison of formula groups at each visit. The test for treatment effect of the score for the gastrointestinal characteristic or general disposition over the 16-week period will have the following hypotheses:

H0: There is no difference between the formula groups.

H1: There is a difference between the formula groups.

If departure from normality is detected, then the gastrointestinal characteristic or general disposition responses will be summarized by frequencies and percentages for each category by formula group and visit. Formula groups will be compared using a Multinomial Logistic Regression model with sex, age at enrollment, baseline value, formula, pooled site, visit, formula by pooled site interaction, and formula by visit interaction as factors. The default SAS covariance structure matrix (independent) for this model will be used. In addition, the formula effect by visit will be summarized. An alpha level of 0.05 will be used to test the formula effect. 95% confidence intervals and p-values will be reported on the odds ratio to compare formula groups at each visit. The test

for treatment effect of the score for the gastrointestinal characteristic or general disposition over the 16-week period will have the following hypotheses:

$H_0$ : Odds Ratio for formula groups = 1, no difference between the formula groups.

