#### **11.2.4. Fussiness**

Two separate questions for fussiness will be assessed and reported at each visit. Fussiness in the past 24 hours will be coded as: 0=Not at all fussy, 1=Slightly fussy, 2=Moderately fussy, 3=Very fussy, and 4=Extremely fussy. Over the past 24 hours, fussiness compared to normal will be coded as: 0=Less fussy than normal, 1=About the same level of fussiness as always, and 2=More fussy than normal. Each score for fussiness over the 16-week study will be analyzed as described in section 11.2.

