#### 11.2.6. Infant Characteristics Questionnaire (ICQ)

The Infant Characteristics Questionnaire (ICQ) was administered at visits 1, 2, 3, 5, 7, and 9. The ICQ (Appendix A) was developed as a short, factor-analytic screening device for difficultness (Bates et al., 1979). The data from the 24-item questionnaire will be summarized into four subscales: Fussy-difficult, Unadaptable, Dull, and Unpredictable. Based on the examination of the factor structure of the items, the authors of the ICQ composed scales using only the discriminating items for use with their normative sample. These scales are composed as follows:

- Fussy/Difficult: Items 1, 5, 6, 13, 22, and 24
- Unadaptable: Items 9, 10, 11, and 20
- Dull: Items 15 (reverse-coded), 16, and 23
- Unpredictable: Items 2, 3, and 4

The sum of the responses for each of the items above comprise the score for each scale. A response for each item is required to calculate a sum score, otherwise the sum score will be set to missing. Higher scores indicate a more difficult temperament. ICQ scales will be summarized by study visits at study sites. Study visits are planned to occur every 15 or 30 (+/- 3) days. A window will be applied to each visit to ensure that subjects are compared at the same formula duration.

| Analysis Visit | Target Day | Window    |
|----------------|------------|-----------|
| 1              | 0          | N/A       |
| 2              | 15         | 8 – 22    |
| 3              | 30         | 23 – 44   |
| 5              | 60         | 45 – 74   |
| 7              | 90         | 75 – 104  |
| 9              | 120        | 105 – 134 |

If more than 1 visit falls within a window, then the visit closest to the target day will be used in the analysis. If more than one visit falls within a window and they are the same distance to the target day, then the latest visit will be used in the analysis. Unscheduled assessments will be assigned to the associated visit based on date and time of assessment.

The scores of the four subscales will be summarized separately by formula group with descriptive statistics at each of the 6 visits. The test for treatment effect of each score over the 16-week study will have the following hypotheses:

H0: There is no difference between the formula groups.

H1: There is a difference between the formula groups.

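### SAP section 11.2's fallback model for repeated GI scores specifies an independent covariance but no infant-level cluster or robust variance, which leaves the size of its 16-week test undetermined

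*Supplement*

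**What the plan says.** SAP V4 section 11.2 has two branches for GI tolerance, the secondary safety objective.

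- **Residuals look normal on a histogram and Q-Q plot.** The scores go to an MMRM whose covariance matrix is selected by AIC, so correlation within an infant is modelled.
- **Otherwise.** "If departure from normality is detected, then the gastrointestinal characteristic or general disposition responses will be summarized by frequencies and percentages". Then: "Formula groups will be compared using a Multinomial Logistic Regression model with sex, age at enrollment, baseline value, formula, pooled site, visit", with formula-by-pooled-site and formula-by-visit interactions added. On covariance the text says only: "The default SAS covariance structure matrix (independent) for this model will be used".

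The null in the second branch, framed over the 16-week period, is: "Odds Ratio for formula groups = 1, no difference between the formula groups". The level is given by: "An alpha level of 0.05 will be used to test the formula effect". Confidence intervals and p-values for the odds ratio are promised at each visit.

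The item sections send their scores to this text. For fussiness, for example: "Each score for fussiness over the 16-week study will be analyzed as described in section 11.2". Stool number and stool consistency (sections 11.2.2 and 11.2.3) and gas (11.2.5) do the same.

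**The concern.** Formula does not change within an infant, so a pooled formula effect is a between-infant comparison. If one infant's scores resemble each other, eight records carry less information than eight records from eight infants. A variance that counts records as independent is then too small. The stated null (odds ratio of 1) does not require an infant's scores to be uncorrelated, yet an independent-records fit uses a reference distribution that does.

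The point estimate is not the issue. What is at stake is a false tolerance difference, in favour of either formula, on the secondary safety objective. Within one section, the error rate would also depend on which branch a visual reading of residual plots selects.

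**Working it through.** **Inputs**
- Two-sided alpha 0.05: SAP 11.2.
- Records per infant: "Nine visits are scheduled at 15-day intervals with a 3-day visit window" (SAP section 3). The flowchart in 4.1 schedules the stool and tolerance questionnaire at all nine. With baseline as a covariate, m = 8.
- Infants: 86 on BBN-102 w/o OPN and 139 on Brand Formula; attrition 25% (SAP section 5).
- Within-infant correlation ρ: not in the documents. Assumed range 0.1-0.5.

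**Closed form.** With an exchangeable correlation and complete records, the variance of the pooled effect is inflated by DEFF = 1 + (m − 1)ρ. An independence-based test then has size 2[1 − Φ(1.96/√DEFF)].

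- ρ = 0: DEFF = 1, size 5.0%. This reproduces the SAP's nominal level under its own independence assumption.
- ρ = 0.1: DEFF = 1.7, 1.96/√1.7 = 1.503, size 13.3%.
- ρ = 0.2: DEFF = 2.4, size 20.6%.
- ρ = 0.3: DEFF = 3.1, 1.96/√3.1 = 1.113, size 26.6%.
- ρ = 0.5: DEFF = 4.5, 1.96/√4.5 = 0.924, size 35.6%.

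The baseline covariate absorbs part of this. Given baseline, the correlation among later scores falls to (ρ − ρ²)/(1 − ρ²) = ρ/(1 + ρ), that is 0.091, 0.231 and 0.333 at ρ = 0.1, 0.3 and 0.5. The sizes become 12.5%, 22.6% and 28.3%.

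**Simulation under the null.** 86 and 139 infants, eight post-baseline visits, 25% dropout, baseline score and visit in a cumulative-logit fit. Entries are rejection rates for the pooled test: model-based / infant-clustered sandwich standard errors.

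| Latent ρ | 5 categories, no formula-by-visit (1000 runs) | 5 categories, with formula-by-visit (700 runs) | 3 categories, with formula-by-visit (700 runs) |
|---|---|---|---|
| 0 | 4.4% / 4.6% | not run | not run |
| 0.1 | 12.0% / 6.3% | 10.9% / 4.6% | 10.3% / 5.7% |
| 0.2 | 16.4% / 6.4% | not run | not run |
| 0.3 | 21.0% / 5.5% | 21.1% / 6.6% | 18.3% / 6.4% |
| 0.5 | 25.7% / 5.4% | 26.7% / 7.0% | 23.6% / 6.7% |

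These lie below the unadjusted closed form because of the baseline covariate, missing visits and the coarsening of scores into categories (a latent 0.5 gives an observed score correlation of about 0.45). At the last visit alone, model-based standard errors gave 4.9-5.7%, as expected with one record per infant.

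**Limits.** Age, pooled site and its interaction were not in the simulated model. Stool number, with 11 response levels, was not simulated. SAP 11.2 says multinomial; a cumulative logit was used because the hypothesis refers to a single odds ratio.

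**The case against.** The strongest reply is that the sentence may already mean something valid. An ordinary logistic fit on separate records has no covariance structure to choose, so the phrase makes most sense as the working structure of a GEE. Independence is then a legitimate choice, and empirical standard errors bring the size close to nominal. This stands as a possible reading. The SAP does not settle it: it names no procedure, no infant-level cluster and no variance estimator. Two programmers could both follow the text and report different p-values for the same safety test.

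Four stronger inferences are tempting and are not supported.

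- **That the plan's test has a false-positive rate of 14-27%.** A simulation without dropout, 600 runs per setting, gave that range. With the SAP's 25% attrition the low end fell to 10-12%. In the no-dropout run at correlation 0.1, even the clustered test rejected 7.5-7.8%, about three Monte Carlo standard errors (0.9 points) above 5%, so its 14-15% there is probably high. Every such figure also depends on an assumed correlation.
- **That the odds-ratio intervals will be too narrow.** The only odds-ratio intervals the SAP promises are per visit, and those are little affected. A 16-week interval would suffer only if someone chose to report one.
- **That all of section 11.2 is exposed.** Stool composition comes from one sample at Visit 9. For the ICQ, "The Infant Characteristics Questionnaire (ICQ) was administered at visits 1, 2, 3, 5, 7, and 9", which leaves five post-baseline scores, and section 11.2.6 gives it its own MMRM with no fallback.
- **That the fallback will be used.** Items with three to five categories make it plausible, but the choice rests on residual plots not yet seen.

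The primary non-inferiority test and the growth endpoints use MMRM and are untouched.

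**Conclusion.** The concern holds as an under-specified variance with a material consequence under the literal reading. If normality fails and model-based standard errors are used, the pooled 16-week test for stool number, stool consistency, fussiness and gas would reject a true null roughly 10-27% of the time instead of 5%. That rests on an assumed within-infant correlation of 0.1-0.5, up to eight post-baseline records per infant and 25% attrition. Even at 0.1 the nominal rate about doubles. With infant-clustered sandwich standard errors the simulated size was 4.6-7.0%, so the inflation essentially disappears if that is what the SAP's authors intend. The point should be settled before unblinding, because it affects a secondary safety test and the text permits either outcome.

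**What to change.** Replace the covariance sentence in SAP section 11.2 with: *Fit by GEE (cumulative logit) with infant as the cluster, independence working correlation and empirical (sandwich) standard errors for the formula-effect tests, odds ratios, CIs and p-values; model-based standard errors will not be used.* Apply it to every item that takes the fallback. An ordinal mixed model with an infant random intercept is an acceptable alternative.

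The cost is one SAP sentence and a subject-level clustering statement in the program, with no new data. The pooled 16-week test will reach significance less often. If a GEE with empirical standard errors was always intended, the change only records it.

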#### **11.2.1. Stool composition**

For stool composition, stool samples will be collected at the last study visit (visit 9, Day 120) to assess moisture content, total soap fatty acid concentrations, soap palmitic acid (calcium palmitate) concentrations, and calcium concentration. Stool composition values that are below the lower limit of detectability will be set to that lower limit value (for example,  $< 0.05$  mg/g will be replaced with 0.05 ng/mL). Dry weights for each concentration will be summarized by formula group with descriptive statistics. Mean concentrations of the formula groups over the 16-week study will be analyzed as described in section 11.2.

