### **13.1 Biological samples**

A single blood sample (1.0 milliliters) will be collected from each subject via heel stick at the last study visit (visit 9) to assess markers of inflammation (tumor necrosis factor- alpha, interleukin 2, 4, 5, 6, 8, 10, 12, 13, & 17; interleukin 2 receptor, interleukin 1 beta, and interferon gamma). Stool samples will also be collected at the last study visit (visit 9) to assess stool composition (soap fatty acids).

Biological samples will be used exclusively for the purposes outlined in this protocol and for no other purpose.

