Initial 3-day Formula/Diet Record will be recorded for 3 days following the first study visit. Remainder of 3-day Formula/Diet Records will be recorded for 3 days prior to each subsequent scheduled study visit.

Blood collection to assess markers of inflammation (tumor necrosis factor-alpha, interleukin 2, 4, 5, 6, 8, 10, 12, 13, & 17; interleukin 2 receptor, interleukin 1 beta, and interferon gamma) and albumin.

Stool collection to assess stool composition. Stool collection supplies will be distributed to parents at Visit 7 for collection of all stools in the 3 days just before Visit 9. The stool collection kit is returned at Visit 9.

Initial telephone contact will occur 3 days after enrollment to check compliance with study feeding and inquire about subject well-being. Remainder of telephone contacts will occur mid-way between clinic visits. Telephone contact notes will be recorded in the study subject's medical record.

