### **6.3. Baseline Values**

Unless otherwise noted, baseline is defined as the last non-missing value recorded prior to the first feeding of the assigned formula.

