### 9.3.1. Markers of Inflammation

A single blood sample (of at least 0.5 milliliters but not more than 0.8 milliliters) will be collected from each subject via heel stick at the last study visit (visit 9, Day 120) to assess markers of inflammation (tumor necrosis factor-alpha, interleukin 2, 4, 5, 6, 8, 10, 12, 13, and 17; interleukin 2 receptor, interleukin 1 beta, and interferon gamma). Biomarker values that are below the lower limit of detectability will be set to that lower limit value (for example, < 5 ng/mL will be replaced with 5 ng/mL). Summary statistics for these biomarkers will be summarized separately by formula group. Formula groups will be compared using a two-sample t-test with 95% confidence intervals and p-values to test the following hypotheses:

H0: The mean values for the marker of inflammation for each formula group is equal.

H1: The mean values for the marker of inflammation for each formula group is not equal.

No adjustment for alpha will be made for these exploratory endpoints.

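### Stool composition is sampled once, at Visit 9 with no baseline, yet SAP V4 sends it to models that need baseline and visit terms, so no workable between-group comparison is specified

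*Supplement*

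**What the plan says.** **Sampling.** SAP V4 section 11.2.1 says that "stool samples will be collected at the last study visit (visit 9, Day 120"), for moisture, total soap fatty acids, soap palmitic acid and calcium. Protocol v5.2 section 13.1 agrees: "Stool samples will also be collected at the last study visit (visit 9) to assess stool composition (soap fatty acids"). The flowchart footnote in SAP section 4.1 adds: "Stool collection supplies will be distributed to parents at Visit 7 for collection of all stools in the 3 days just before Visit 9".

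**Analysis.** Section 11.2.1 sets values below the detection limit to that limit, asks for descriptive statistics by formula group, and continues: "Mean concentrations of the formula groups over the 16-week study will be analyzed as described in section 11.2". Section 11.2 then offers two routes, chosen from plots of studentized residuals.

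- If residuals look normal: "Treatment effect will be compared using a mixed-effect model for repeated measures (MMRM) with sex, age, baseline value, formula, pooled site, visit", plus formula by pooled site and formula by visit.
- If not, responses are tabulated by category and "Formula groups will be compared using a Multinomial Logistic Regression model", again with baseline value, visit and formula by visit, reported as odds ratios.

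**Rules that bear on this.**

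- Section 6.3: "baseline is defined as the last non-missing value recorded prior to the first feeding of the assigned formula".
- Section 6.8 lets one term be dropped if a model does not converge: formula by pooled site.
- Section 6.4 plans, in general, no imputation.
- Section 2.2.5 lists stool composition first among the components to be compared between groups under the secondary safety objective.

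**The concern.** Section 11.2 was written for questionnaire items and scores recorded at Visit 1 and repeatedly afterwards. Stool composition has a different structure: one sampling occasion per infant, at the end of feeding, with nothing before it. The cross-reference gives it a model whose longitudinal terms have no data behind them. It also speaks of a mean over 16 weeks that was never measured.

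If the instruction cannot be followed, someone must later decide which terms to remove, which scale to use and how to treat values at the detection limit. Those choices can change the estimate and P-value for a named component of the secondary safety objective. Settling such choices in advance is the purpose of the SAP.

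**Working it through.** The documents give no figure for stool composition, so there is nothing to reproduce. The check is whether the specified models can be fitted.

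**Inputs.** The group sizes are the planned 64 (BBN-102 w/o OPN) and 104 (Brand Formula), 168 in total, from SAP section 5. They serve only as an illustration, since the safety population may differ. Two further inputs are assumptions: four pooled sites, and log-normal concentrations (log mean 3, log SD 0.6).

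1. **Terms.** Section 11.2 lists eight: sex, age, baseline value, formula, pooled site, visit, formula by pooled site, formula by visit. Three of them (baseline value, visit, formula by visit) have no content when there is one occasion and no baseline.

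2. **Baseline.** Under section 6.3 a baseline must precede the first study feeding. Kits are dispensed at Visit 7 (Day 90), so every infant's stool baseline is missing. With baseline as a covariate and no imputation, complete records = 0 of 168. The normality check fails too, because there is no fitted model to supply residuals.

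3. **Visit.** Suppose baseline is removed. The remaining fixed effects have rank 1 (intercept) + 1 (sex) + 1 (age) + 1 (formula) + 3 (site) + 3 (formula by site) = 10. Adding the 3 columns for visit and formula by visit leaves the rank at 10. These terms are redundant, and software would alias them. With one record per infant there is also no within-infant covariance for AIC to choose.

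4. **Fallback.** It keeps the baseline term, so step 2 applies again. Beyond that, no cut-points turn a concentration into categories. In the simulated data the number of distinct values among 168 infants was:

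| Rounding | Distinct values | Generalized logit, (k − 1) × 10 parameters | Cumulative logit, (k − 1) + 9 parameters |
|---|---|---|---|
| 2 decimals | 167 | 1,660 | 175 |
| 1 decimal | 134 | 1,330 | 142 |
| whole numbers | 44 | 430 | 52 |

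   The SAP does not name the logit. A generalized-logit model has more parameters than infants at every rounding shown. The cumulative-logit counts are mostly intercepts and are taken up under the objection.

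5. **Early withdrawal.** Protocol section 21 asks for Visit 9 procedures when an infant withdraws, so some samples may fall in another analysis window. Each infant still has one sampling occasion and no baseline, so steps 1, 2 and 4 stand.

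**The case against.** The strongest reply is that this is a loose cross-reference which any programmer would resolve sensibly. The visit terms drop out by themselves, the non-existent baseline is left out, and what remains is a Visit 9 linear model close to the one proposed below. That is right about the visit terms, which are not fatal. It does not cover baseline: section 6.8 permits a different term to be dropped, and nothing permits this one. The reduced model would be reasonable, but it would be an improvised choice, with scale and treatment of detection-limit values still open.

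On the fallback, a cumulative-logit model with one level per distinct value can work as a rank-type method for continuous data. The SAP does not say that this is meant. It asks for frequencies by category, and it keeps the baseline term.

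A reader might also infer more than the documents support:

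- **That stool composition has no analysis at all.** The descriptive summary by group in section 11.2.1 can be produced as written.
- **That the comparison will certainly be settled after seeing the data.** Section 6 labels analyses made after unblinding as post hoc, and section 12 requires an amendment or addendum for added summaries. The gap can still be closed properly.
- **That the same fallback inflates type I error for the repeated tolerance items.** Section 11.2 names an independent covariance but not the type of standard error. With empirical errors clustered on infant, the overall test would be approximately valid, and comparisons at a single visit use one record per infant. Inflation would require model-based errors and would concern the overall 16-week test only.
- **That the cytokine t-tests are invalid.** For the cytokines, section 9.3.1 says "Biomarker values that are below the lower limit of detectability will be set to that lower limit value" and tests on the raw scale. These endpoints are exploratory. Any loss of power depends on spread and censoring that the documents do not give. The protocol's remark on geometric means (section 14.1.3) does not say that cytokines will be log-transformed.

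**Conclusion.** The point holds for the between-group comparison of all four stool measures. As written, neither section 11.2 model can be applied: baseline is required and cannot exist, visit has no role, and the non-normality route is designed for categories. Three of eight terms are empty and no record is complete.

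The conclusion about baseline follows from the documents alone and does not depend on sample size or distribution. Only the counts of distinct values and parameters rest on the simulated concentrations and the assumed four pooled sites.

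The reach is limited. Stool composition is one component of a secondary safety objective, the descriptive summary survives, and the weight-gain analysis is untouched. It should be corrected, but it does not threaten the trial's main conclusion.

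**What to change.** In SAP section 11.2.1, replace the cross-reference and the reference to a mean over 16 weeks with a self-contained analysis:

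- One linear model at Visit 9 with formula, sex, age at enrollment and pooled site, and no baseline, visit or formula-by-visit terms.
- Soap fatty acids, soap palmitic acid and calcium on the log scale, reported as a ratio of geometric means with 95% CI. Moisture untransformed, reported as a difference in means with 95% CI.
- A Wilcoxon rank-sum test as the fallback for an analyte when the proportion of its values below the detection limit exceeds a threshold. Write that threshold into the SAP before unblinding. A phrase such as many values below the limit would leave the choice open again.
- A sentence saying whether samples taken at early withdrawal are included.

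Remove stool composition from the endpoint list in section 11.2. For the ordinal tolerance items that stay there, one clarifying sentence is enough: the independence working structure is used with empirical standard errors clustered on infant.

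The cost is SAP wording. No new data are needed, and the programs are simpler than those now described. If the blind has already been broken, the same analysis can be run but should be labelled post hoc, as section 6 requires.
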